**Methods:**

In a single-armed intervention trial (*N* = 40) children aged 8–14 years with a primary diagnosis of ARFID and their caregivers will receive a digital cognitive-behavioral therapy. The intervention consists of a 12-session program, combining video therapy sessions with children and caregivers and self-guided modules. Assessments occur at baseline, mid-treatment, post-treatment, and 4-week follow-up with additional symptom monitoring questionnaires per session. Primary outcomes include feasibility, recruitment and retention rate. Secondary outcomes include ARFID symptoms (e.g., Eating Disorder Examination ARFID module, Nine Item Avoidant/Restrictive Food Intake Disorder screen), food neophobia (Food Neophobia Scale) and quality of life (Generic Quality of Life Instrument for Children-Revised).

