Cognitive behavioral therapy interventions have also shown promise for treating ARFID. A clinical case series of children ages 10–18 years with ARFID who received CBT for ARFID delivered in a day treatment setting demonstrated that 10 out of 11 children were in remission at three-month follow-up (13). Furthermore, Thomas & Eddy (2019) developed an outpatient manualized Cognitive-Behavioral Therapy for Avoidant/restrictive food intake disorder (CBT-AR (14)) that they and others have now tested in two open trials (12, 15) and several case studies (16–18). CBT-AR was developed for children, adolescents and adults from the age of 10 years and leverages food exposure as the key intervention. It is delivered in an individual or family supported format, with the latter being recommended for children and adolescents under the age of 16 or older adolescents who are underweight (14). Two studies showed that CBT-AR is feasible as well as acceptable in both pediatric (15) and adult (12) patients, demonstrating evidence for proof of concept (12, 15). In the pediatric sample, 70% achieved remission at post treatment and patients incorporated an average of 16.7 new foods in their diet (15). Moreover, CBT-AR suggests different exposure-based treatment strategies tailored to the three different presentations of ARFID (sensory sensitivity, lack of interest in eating or food or fear of negative consequences), making it flexible to adapt to patient specific presentations. Importantly, patients with sensory sensitivity showed significantly greater improvement when receiving the targeted intervention for this presentations compared to those who did not receive the presentation-specific intervention in a CBT-AR intervention study (19). To our knowledge, none of the previous cited interventions have been evaluated in German speaking countries where ARFID prevalence has been established (4, 20, 21), and specialized treatment services are currently lacking.

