1	1	Clinican-delivered video-therapy	Psychoeducation: Symptoms of ARFID, CBT-AR treatment structure, development of individual ARFID formulation	Starting a parent-monitored food diary, adopting a regular eating schedule, establishing first small changes in eating behaviors
2	2	Self-guided session	Psychoeducation on balanced diet, risk of nutritional deficiencies, planning food exposure tasting session	Identifying underrepresentation of food groups in child’s diet, choosing foods for food exposure. Optional: Creating a reward schedule
3a	3	Clinican-delivered video-therapy	Food-Exposure tasting session	Food-Exposure tasting session and starting an exposure tracker
3a	4	Self-guided session	Additional tips for food-exposure sessions; strategies of integrating new foods (part 1)	Food-Exposure tasting session, tracking of exposure and integrations of foods
3a	5	Clinican-delivered video-therapy	Food-Exposure tasting session	Food-Exposure tasting session, tracking of exposure and integrations of foods
3a	6	Self-guided session	Food-Exposure tasting session, strategies of integrating new foods	Food-Exposure tasting session, tracking of exposure and integrations of foods
3a	7	Clinican-delivered video-therapy	Food exposure tasting session and troubleshooting of integrating new foods	Food-Exposure tasting session, tracking of exposure and integrations of foods
3b	8-11	Self-guided session and chat feedback	Food exposure tasting sessions and integration of accepted new foods	Food-Exposure tasting session, tracking of exposure and integrations of foods
4	12	Clinican-delivered video-therapy	Planning of further recovery steps; potential difficulties and relapse prevention	

ARFID, avoidant/restrictive food intake disorder. CBT-AR, Cognitive-Behavioral Therapy for Avoidant/restrictive food intake disorder.

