### Assessment and data management

2.7

We will assess at screening (t0), baseline (t1), mid-intervention after completion of session 6(t2), post-intervention after completion of session 12(t3) and 4-week follow-up (t4). We will use German translations of all questionnaires. Additionally, parents/guardians will complete brief weekly measures after every session. Self-report data will be assessed via Qualtrics (i.e., for outcome measures, Qualtrics, 2025) and participants will be asked to provide only their assigned participant code when answering the questions. Only the internal study team will have access to the key file in digital password protected folder to link the participants code to the names. Additionally, the secure health platform Curafida (ZTM Bad Kissingen GmbH, 2025) will integrate the software MyMedax for content and reflection questions in self-guided sessions. We will use the secure video call software webPRAX for video call sessions (Healthy Projects GmbH, n.d.). We created a data protection policy and a register of all processing activities with the legal office of Konstanz University for this study. Moreover, a data protection and confidentiality agreement will be in place between the company of the health platform ZTM Bad Kissingen GmbH and the University of Konstanz.

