Diagnostic Interview for Mental Disorders in Children and Adolescents	(36)	Diagnosis of comorbid symptoms (DSM-5)			Criterion fulfilled yes/partially/no		x								
Children’s Depression Screeners (ChilD-S)	(46)	Depression	8		4 Point Likert scale; 0 = “agree” to 3 = “disagree”							x	x	x	x
State–Trait Anxiety Inventory—Child version trait subscale	(47)	Trait Anxiety	20		3-response scale							x	x	x	x
Generic Quality of Life Instrument for Children-Revised-	(51)	Health-related quality of life	24	Physical well-being psychological wellbeing, self-esteem, family, friends, education/school	5-point Likert scale from 0 = “never” to 4 = “always”							x	x	x	x
Working alliance inventory—short revised	(52, 53)	Therapeutic alliance	12		5-point Likert scale from 1 = “rarely” to 5 “always”			x	x	x					
Therapeutic Alliance Scales for Children	(54)	Therapeutic alliance	12	Bond/working alliance; Positive and negative aspects of the emotional bond	4-Point Likert scale from 1 = “not at all” to 4 = exactly right”								x	x	x
Additional measures															
Children Eating Disorder Examination-Questionnaire (EDE-Q8)	(55, 56)	eating disorder psychopathology	8	restraint, eating concern, weight concern, and shape concern	0–6 scale = number of days in the previous 28; or (b) “Not at all” to “Markedly, ratio scale	x						x	x	x	x
Children Eating Disorder Examination-Questionnaire Parent version (EDE-QP-parent version)	(56)	eating disorder psychopathology	28	restraint, eating concern, weight concern, and shape concern	0–6 scale = number of days in the previous 28; or (b) “Not at all” to “Markedly, ratio scale	x									
The Affinity for Technology Interaction (ATI) Scale	(57)	Affinity for Technology Interaction	9		6-point Likert scale, 1 = “strongly disagree” to 6 = “strongly agree”		x								

ARFID, avoidant/restrictive food intake disorder. Assessment will take place at screening (t0), baseline (t1), mid-intervention (t2), post-intervention (t3) and 4-week follow-up (t4). Additionally, parents will be asked to fill out weekly the FNS; NIAS, and adverse event scale. Furthermore, number of integrated new foods will be tracked by caregivers from week 3 onwards. Demographic characteristics (e.g., gender, age) will be assessed at screening and baseline and parent-child interaction regarding food at pre-, mid and post-treatment.

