### Proposed statistical analysis

2.10

As our primary aim is to assess feasibility, we will report recruitment rates and retention rates and number of adverse events until post-assessment with descriptive statistics. We will also report feasibility ratings of parents regarding the duration of sessions and materials, number of foods tasted per week, as well as the overall therapy duration of individuals completing the intervention. Acceptability will be descriptively reported based on parents rating on the treatment credibility (Credibility/Expectancy Questionnaire (CEQ) (48) and treatment satisfaction (Client Satisfaction Questionnaire (CSQ) (49)), as well as single-items for children.

As a secondary aim we will analyze ARFID symptoms reduction with paired sample t-test for expert-rated psychosocial impairment and sensory sensitivity (based on the Eating Disorder Examination (EDE) ARFID module, as well as self-report measures of symptoms of ARFID (i.e., Nine Item Avoidant/Restrictive Food Intake disorder screen (NIAS) (43) and Food Neophobic Scale (FNS) (44)) and children’s quality of life will be conducted from pre- to post assessments and pre-to follow-up.

Exploratory, in line with previous research we will also analyze anxiety (STAI (47)) and depression levels (Children’s Depression Screeners (46)) using dependent t-tests to test for potential changes in comorbid symptoms (12, 15).

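### Caregiver NIAS and FNS are collected after every session but tested only at two time points, so the planned analysis cannot place change before or after the first tasting and drops families lost before post-assessment

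*Protocol article*

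**What the plan says.** Section 2.7 states that "parents/guardians will complete brief weekly measures after every session". The note to Table 2 names the instruments: "parents will be asked to fill out weekly the FNS; NIAS, and adverse event scale". The abstract likewise lists the four assessments "with additional symptom monitoring questionnaires per session". Table 2 also schedules caregiver NIAS and FNS at t0 to t4, and section 2.7 places t2 after session 6 and t3 after session 12.

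Section 2.10 fixes the analysis: "we will analyze ARFID symptoms reduction with paired sample t-test". The comparisons "will be conducted from pre- to post assessments and pre-to follow-up". No analysis is named for the session series or for the t2 readings of these two instruments.

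The Introduction says that CBT-AR "leverages food exposure as the key intervention". In Table 1, sessions 1 and 2 are psychoeducation and planning. The first tasting is in session 3, whose homework is "Food-Exposure tasting session and starting an exposure tracker".

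**The concern.** The trial has one arm, and its secondary purposes are proof of concept and effect sizes for a later randomised trial (sections 2.3 and 2.9.1). Without a control group, the timing of change relative to the start of exposure is one of the few internal checks available. It describes whether scores moved when the exposure content was delivered or already during enrolment and psychoeducation. The t2 reading cannot help, because exposure is well under way by session 6. Of the readings taken once treatment has started, only those after sessions 1 and 2 precede the first tasting, and the stated tests use neither.

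A paired test also needs both members of the pair. Section 2.3 expects 20-30% dropout. A family that leaves after, say, session 8 has a baseline and eight session readings, and none of them enters the pre-to-post comparison.

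**Working it through.** **1. The plan is sized on a two-point comparison.** Inputs from section 2.3: alpha 0.05, power 0.95, effect size 0.6, n = 32. Reading 0.6 as the mean change divided by the SD of the change, the noncentrality is 0.6 × √32 = 3.39 on 31 degrees of freedom. One-sided power is 0.953, and 32 is the smallest n that reaches 0.95, so the stated figure is reproduced. Two-sided power at n = 32 is 0.908.

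**2. What the paired test can see.** Write the change as D = (reading after session 2 − t1) + (t3 − reading after session 2). The test uses D only. A course with the whole fall in the first bracket and one with the whole fall in the second give the same D. Simulation with 32 completers, a mean change of 0.6 SD of the change score, and assumed single-occasion error variance of 0.1 to 0.3 of the change-score variance:

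| Contrast (two-sided 5%) | All change by session 2 | All change from session 3 |
|---|---|---|
| Planned t1 to t3 | about 90-92% significant | about 90-92% significant |
| t1 to session 2 | about 91% | about 3% |
| Session 2 to session 12 | about 2% | about 90-91% |

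The two columns are deliberate extremes. They show that the planned test cannot distinguish them. They do not show how sharply a gradual course would be resolved.

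**3. Precision with complete data.** Let V be the covariance matrix of one family's readings and c the contrast (−1 at t1, +1 at t3). With a free mean at each occasion and n complete families, the information matrix is nV⁻¹, so the contrast variance is c′Vc/n. That is the variance of the paired difference, so there is no gain.

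**4. Precision with dropout.** Assumptions: 40 enrolled; 10 lost (25%, inside the expected range), with last readings spread over sessions 2 to 9; readings at 0 to 12; dropout explained by observed readings; V known. The protocol gives no covariance, so three are assumed. Paired SE = √(variance of the difference / 30). Model SE = √(c′I⁻¹c), where I sums each family's information over its observed readings.

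| Assumed covariance | Variance of difference | Paired SE (30) | Free-mean model SE | Ratio |
|---|---|---|---|---|
| Random intercept 0.5, error 0.5 | 2 × 0.5 = 1.0 | 0.183 | 0.173 | 0.946 |
| Intercept 0.6, slope 0.4, error 0.4 | 0.4 + 2 × 0.4 = 1.2 | 0.200 | 0.189 | 0.944 |
| Intercept 0.6, slope 0.8, error 0.2 | 0.8 + 2 × 0.2 = 1.2 | 0.200 | 0.186 | 0.932 |

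The SE falls by about 5-7%. In completer terms, 30 / 0.946² = 33.5 and 30 / 0.932² = 34.5, so the partial data are worth roughly four families.

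**5. Why the mean should not be forced into two straight lines.** A line with one change of slope after session 2 was fitted by least squares to noiseless courses with a true total fall of 1:

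- Fall linear over sessions 2 to 12, then maintained, with t4 (week 16) included: the t1-to-t3 fall is estimated as 0.90, about 10% too small.
- Fall linear over sessions 2 to 7, then flat, with t4 included: 0.38 of the fall is placed before the first tasting, where the truth is 0, and the total is 12% too large. Without t4 these figures are 0.26 and 28%.

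So a purely post-tasting fall would be reported partly as pre-tasting. A separate mean per occasion avoids this.

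**The case against.** The strongest reply is that section 2.10 contains no error. It does not say that the session forms will go unused, and a condensed article may leave their modelling to a fuller plan. The Introduction hypothesises reduction from pre- to post-intervention and asks whether effects last to follow-up, and paired t-tests answer both. Timing relative to the first tasting is not a stated aim. This stands in part: the planned tests suit the stated hypotheses, and timing can only be an added, exploratory question. It does not remove the point, because 2.10 is not silent on method. For these very instruments it names the test and both contrasts, and that choice leaves out the readings that families are asked to supply.

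A second reply is that the contrast would not isolate exposure. This stands. Session 1 homework already asks for a regular eating schedule and initial small changes in eating, and session 2 plans the tasting. At the recommended pace the two periods last about 2 and 10 weeks and differ in therapist contact.

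Three stronger readings are tempting, and the documents do not support them:

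- That the trial cannot show the timing of change. It can, because the data are collected; only the planned analysis cannot.
- That the plan gives up substantial precision even with complete data. Such a gain appears only when a shape is imposed on the mean. For a two-segment line the SE ratio ran from 0.73 to 1.00 depending on the assumed covariance, with the bias shown in step 5.
- That change after the first tasting would itself establish proof of concept. In a single arm it describes timing and not cause.

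**Conclusion.** The point holds as a cheap improvement to a stated analysis; it does not invalidate the plan. For caregiver NIAS and FNS, the paired t-tests cannot place change before or after the first tasting, and the pre-to-post test discards families lost before t3. The timing argument follows from Table 1 and section 2.10 alone. The precision argument is smaller: an SE about 5-7% lower with 10 of 40 families lost, and none with complete data. It rests on assumed covariances and on dropout being explained by observed readings.

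The expert-rated ChEDE module (t1 and t3 only), quality of life and child reports have no session series and are unaffected. Feasibility remains the primary aim, and section 2.3 already warns that power may not support conclusions about efficacy.

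**What to change.** Add to section 2.10, for caregiver NIAS and FNS only: a linear mixed model with time as a categorical factor, that is, a separate mean at each occasion with no slope or knot imposed on the means, including every family with any reading. Report with 95% confidence intervals:

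- (a) t1 to the last reading before the first tasting;
- (b) that reading to t3;
- (c) t1 to t3;
- (d) t1 to t4.

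State that (a) and (b) are exploratory and describe timing, that sessions 1 and 2 are not an untreated period, that the two periods differ in length, and that neither contrast is a control or carries the proof-of-concept conclusion by itself. Keep the paired t-tests for the ChEDE and other outcomes without a session series, and as supporting analyses for NIAS and FNS.

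Name a structured covariance in advance, for example random intercept and slope. If the session 6 and 12 forms coincide with t2 and t3, there are 14 occasions (t1, 12 sessions, t4), and an unstructured matrix would need 14 × 15 / 2 = 105 parameters from 40 families.

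Cost: a few sentences and one extra model, with no new visits, forms or families. The downside is more parameters in a small sample, for a benefit limited to the FNS and to a NIAS that the protocol says is not yet validated in German.

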## Discussion

3

The aim of this feasibility trial is to evaluate the feasibility and proof of concept of a therapist-guided cognitive therapy intervention for children with ARFID and their parents/guardians.

This ExpeditionFood intervention is based on the manualized CBT-AR treatment which has been shown to be feasible in a face-to face intervention format in children and adolescents (15). The intervention could help to overcome some of the treatment barriers (22, 23) for ARFID by making the CBT-AR more accessible in regions with less specialized treatment services and including mostly self-guided sessions allowing for more flexible timing of sessions.

The current design has several strengths. First of all, the digital format and emphasis on self-guided session allows families to be more flexible in their participation, increases accessibility and can reduce commute and family time constrains. Moreover, this is the first ARFID specific intervention translated to German making CBT-AR available in German speaking countries where ARFID specific interventions are lacking.

However, the current design also has some limitations. First, we opted to focus this standardized short intervention only on the sensory sensitivity presentation of ARFID. Although this will provide preliminary insight into the feasibility of a standardized digital intervention, it will also limit the generalizability of the findings to other presentations of ARFID. Additionally, we decided to focus on a rather young age range compared to previous CBT-AR trials, as parents/guardians might play a more central role than in older age ranges. Further extensions and adaptations may be needed for older adolescents and adults or for children with a neurodiversity, and might be tested in follow-up studies to this pilot trial. Further, multiple case reports have suggested that CBT-AR can be delivered with good outcomes to individuals with neurodivergent profiles (17, 50). To provide additional support for the personalized ARFID formulation and the administration of food exposures, we have incorporated video therapy sessions with a study therapist. While this prevents the stand-alone use of the digital intervention at the moment, the majority of the intervention can be still conducted in a self-guided manner. Similarly, we opted for non-standardized messages in the third intervention stage to help families addressing potential challenges related to food exposure. While this requires the availability of a study therapist and might reduce generalizability and may not be as economical as possible, it may also increase engagement in the intervention and reduce drop out. Lastly as this is the first intervention study in Germany and commonly used self-report measures (i.e., NIAS) assessing symptoms of ARFID are currently not yet validated in German, the findings will have to be interpreted bearing this limitation in mind.

## Conclusion

4

ARFID is mostly common in children and is associated with severe health consequences. However, families with children with ARFID report various treatment barriers and long treatment journeys, suggesting a need for flexible and low-threshold interventions. Cognitive-behavioral therapy has shown to be feasible in face-to-face trials supporting proof-of-concept. However, intervention studies for ARFID and specialized treatment services in German-speaking countries are lacking. The present study will aim to investigate the feasibility of CBT-AR delivered as a therapist guided digital intervention and investigate the proof of concept in a parent-guided format. The present study has the potential to inform further clinical trials on digital delivery of interventions for ARFID.
